### Inclusion criteria

Intractable neuropathic pain resistant to drug treatment using more than one drug.Age ≥ 18 years.Pain visual analog scale (VAS) score > 40.Written, informed consent.

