#### SF-MPQ-2

The SF-MPQ-2 consisted of 22 items to provide increased responsiveness [22]. Each item is evaluated with an 11-point scale (0 representing no pain and 10 representing the worst pain imaginable). The SF-MPQ-2 is divided into 4 subscales, including 3 sensory descriptors and 1 affective descriptor, as follows: continuous pain descriptors (6 items), intermittent pain descriptors (6 items), predominantly neuropathic pain descriptors (6 items), and affective descriptors (4 items). The total pain dimension parameter is the sum of the sensory and the affective dimension of the pain (score range: 0 to 220). A high score indicates a high level of pain.

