#### PCS

The PCS is used to measure pain-related catastrophic thoughts and consisted of 13 items [23]. Each item is scored on a 5-point Likert scale; evaluations (0 = not at all to 4 = always) are made. The scale assesses catastrophic thinking/feeling regarding 3 components: rumination, magnification, and helplessness. The total score range is from 0 to 52 points, and a higher score indicates a higher level of pain-related catastrophic thoughts.

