#### QIDS-J

The QIDS-J consists of 16 questions and plays a role in the diagnostic criteria for major depressive disorder [24]. These questions are divided into nine categories. Four concerned sleeping disorders, four appetite and body weight, two psychological disorders, and the remaining nine other topics. The total score range is from 0 to 48 points, and a higher score indicates a higher level of depressive disorder.

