The secondary outcome will be analyzed as follows:Similar analyses of the primary outcome analysis will be performed for each causative disease.Comparison of DTM and FAST stimulation patterns for pain improvement in Stim-3. Pain improvements will be compared between DTM and FAST stimulations using logistic regression analysis adjusted for the treatment group (DTM stimulation, FAST stimulation) and pre-VAS value. Similar analyses will be performed by causative disease.Adjusted mean values and 95% confidence intervals of changes in assessment items including the VAS, SF-MPQ-2, PCS, and QIDS-J before the SCS system implantation, and at 1, 3, 6, 12, 18, and 24 months after SCS system implantation at each time point will be calculated using a linear mixed model with the interaction between treatment group and time point as a fixed effect. Analysis will be performed using a linear mixed model with the change rate and change amount of each indicator as outcome variables. The rate and amount of changes in each index at each evaluation time point will be compared between groups using fixed effects such as pretreatment value of each index, treatment group, evaluation time point, and interaction between the treatment group and evaluation time point. The 12-month analysis will be performed at preoperative, 1, 3, 6, and 12 months, and the 24-month analysis will be performed at 18 months and the final follow-up (24 months).In participants with no missing VAS values preoperatively to 12 months after implantation, analyses of the prognostic factors related to the long-term effect of continuing 33% reduction in the pain VAS over 12 months will be performed using logistic analysis with the following explanatory variables: treatment group, pre-implantation VAS value, sex, age, causative disease, site of pain, degree of paralysis, degree of sensory disturbance, and disease duration.

A comparison between the new and conventional stimulation patterns will be performed with Stim-1and Stim-2. A comparison between DTM and FAST, which is the new stimulation pattern, will be performed with Stim-3. Therefore, this study is designed to compare the VAS improvement rates in different stimulation patterns, so it is not necessary to consider multiplicity.

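### Individual percent change as a model outcome for QIDS-J and PCS, whose scores can start at 0, understates mean improvement and costs power (minor)

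*Protocol article*

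**What the plan says.** The Statistical analysis section covers "changes in assessment items including the VAS, SF-MPQ-2, PCS, and QIDS-J" before implantation and at six visits up to 24 months. It then states: "Analysis will be performed using a linear mixed model with the change rate and change amount of each indicator as outcome variables". Groups are compared with "fixed effects such as pretreatment value of each index, treatment group, evaluation time point, and interaction between the treatment group and evaluation time point".

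All three questionnaires include 0. For PCS, "The total score range is from 0 to 52 points"; for QIDS-J, "The total score range is from 0 to 48 points"; for SF-MPQ-2, "score range: 0 to 220". High scores are unfavourable (for QIDS-J, "a higher score indicates a higher level of depressive disorder"), so a fall is an improvement.

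The only score required for entry is "Pain visual analog scale (VAS) score > 40". No criterion asks for depressive symptoms or catastrophizing.

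The article does not define the change rate. Percent change from the pre-implantation value is the natural reading, and it matches the 33% VAS rule under Secondary outcomes. The Discussion notes that outcomes 3 and 4 cover responders only and gives them reference status.

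**The concern.** A ratio to each patient's own baseline needs a baseline well away from 0. The VAS entry threshold largely secures that for VAS. Nothing secures it for QIDS-J or PCS, and a patient in severe pain may have few depressive symptoms. Three problems follow.

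- A baseline of 0 gives no change rate.
- A fall stops at -100%, while a rise from a small baseline is nearly unbounded. Random variation alone therefore gives a positive mean.
- The outcome is skewed, and its variance is largest at low baselines. That suits a normal linear mixed model poorly. A linear term for the pretreatment value neither creates a value at baseline 0 nor removes the skew.

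At stake are the adjusted mean change rates for mental state, their confidence intervals and the power of the group comparisons.

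**Working it through.** **The plan's own figure.** The article gives none for this analysis. The sample size of 78 rests on the primary outcome and is not touched.

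**Mechanism.** Change rate = 100 × (follow-up - baseline) / baseline. A rise of 2 points is +200% from 1, +100% from 2, +20% from 10 and +10% from 20. From 0 it is undefined. Take two patients, one going from 1 to 4 (+300%) and one from 20 to 10 (-50%). Their mean change rate is (300 - 50)/2 = +125%, although their summed score fell from 21 to 14. This pair shows the mechanism only and is not a forecast.

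**Expected size, QIDS-J.** Baseline means, SDs and the model are assumptions. Each patient has a gamma-distributed true level. Baseline x and follow-up y are Poisson around it, with the follow-up level multiplied by c (c = 1 for no change, 0.7 for a true 30% fall). The upper end of the scale is ignored. With baseline mean m:

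- correlation under no change: r = (SD² - m)/SD²
- expected follow-up given baseline: c × [m + r(x - m)]
- hence mean change rate among x > 0: c(1 + A) - 1, where A = (1 - r) × (m × E[1/x | x > 0] - 1)

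Baseline x is then negative binomial, which gives E[1/x | x > 0] and the share at 0.

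| Mean/SD | r | m × E[1/x] | No change: A | True 30% fall: 0.7(1 + A) - 1 | Baseline 0 |
|---|---|---|---|---|---|
| 6/4 | 0.625 | 1.590 | +22.1% | -14.5% | 2.9% |
| 8/5 | 0.680 | 1.598 | +19.2% | -16.6% | 1.4% |
| 10/5 | 0.600 | 1.388 | +15.5% | -19.1% | 0.2% |
| 16/6 | 0.556 | 1.183 | +8.1% | -24.3% | 0.0% |
| 20/7 | 0.592 | 1.152 | +6.2% | -25.7% | 0.0% |

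First row: (1 - 0.625) × (1.590 - 1) = 0.221, and 0.7 × 1.221 - 1 = -0.145. The mean change amount is (c - 1) × m, which is 0 under no change. Under the fall it is -0.3m, and divided by m this returns exactly -30%.

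**A second model.** This one uses gamma true scores plus normal error, rounded and truncated to the scale, with no true change.

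- QIDS-J (error SD 2): +10.7%, +11.1%, +6.1% and +2.5% at means 5, 8, 12 and 16, with 12.4%, 4.0%, 0.3% and 0.01% of patients at 0.
- PCS (error SD 4): +16.6%, +6.3% and +2.5% at means 15, 25 and 32 (SD 10, 11, 10), with 4.3%, 0.25% and 0.01% at 0.

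For PCS, the formula above gives 0.15 × (1.787 - 1) = +11.8% at 15/10 and 0.32 × (1.113 - 1) = +3.6% at 32/10. The size depends on the model, but the direction does not.

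**Group comparison.** Assumptions: 35 against 35 patients, one follow-up, linear model adjusted for baseline, gamma-Poisson scores. With a 30% fall in one group only, power is about 0.46, 0.58 and 0.72 for the change rate at 6/4, 8/5 and 10/5. For the change amount it is 0.74, 0.86 and 0.94. At 16/6 the figures are 0.95 and 0.99. With no group difference (no change in both, or a 30% fall in both), the change-rate test rejected in about 4% to 6% of simulated trials, close to the nominal 5%.

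**The case against.** The case against acting has four parts.

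- **A sound analysis is already there.** The change amount, adjusted for the pretreatment value, is planned for every indicator and keeps patients with a baseline of 0. This stands and limits the consequence to one of two planned outputs.
- **Outcome 3 is reference information.** This also stands. But the caveat in the Discussion concerns the absence of non-responders. It does not warn that one of the two summaries is biased.
- **Baselines may be higher than assumed.** True; the documents are silent. At higher means the artefact shrinks but does not vanish.
- **A rule for a zero baseline may sit in an analysis plan not shown.** Possible, so it is not established that such patients would be lost. A rule of that kind would not remove the skew at baselines of 1 or 2, and the choice of outcome is fixed here.

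A reader might infer more than the documents support:

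- **False group differences.** The upward shift affects both groups, and the type I error stays near 5%.
- **Real improvement reported as worsening.** With a true 30% fall the mean change rate is still negative in every scenario. A reversed sign needs a very small effect. In the second model, PCS at an assumed mean of 15 with a true 1-point improvement gave +5.7%, against a mean change of -0.95 points.
- **SF-MPQ-2 equally affected.** Its range also starts at 0, but patients with intractable pain are unlikely to score near 0 on 22 pain items, and no size was derived for it.

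**Conclusion.** The point holds, at minor severity. Following the stated analysis leaves a zero baseline without a value, understates the mean percentage improvement on QIDS-J and PCS, and lowers the power of the change-rate comparison.

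The size depends on baseline levels that the documents do not give. It is appreciable if baselines are low and small if they are high, and at low means it also varies with the assumed score model. The finding rests on reading the change rate as percent change from the pre-implantation value. The 35-against-35 setting with a fall in one group only is also assumed; it illustrates relative power and does not predict this trial. The primary outcome and the sample size are unaffected.

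**What to change.** For QIDS-J and PCS, remove the individual change rate as an outcome of the linear mixed model and rely on the planned change amount adjusted for the pretreatment value. If a percentage is wanted, report the adjusted mean change divided by the mean pretreatment score. Keep the individual change rate for VAS, where the 33% definition uses it. Treating SF-MPQ-2 like the two mental-state scales is optional, for consistency.

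The cost is a change of wording, with no new data, visits or patients. The small downside is that these two scales will have no model of individual percent change.

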### Clinical assessments

On enrollment in this trial, clinical research physicians will obtain information from the patients including age, sex, past history, current medication, causative disease of pain (central post-stroke pain, post–spinal cord injury pain, failed back surgery syndrome, complex regional pain syndrome, post-herpetic neuralgia, diabetic neuropathic pain, peripheral arterial disease, or others), lesion site causing pain (central or peripheral), location of pain (arm, leg, lower back, back, chest, face), laterality of pain (left, right, midline), degree of paralysis (none, mild, moderate, severe), sensory disturbance (hypoesthesia, allodynia, numbness), and duration of disease. During the SCS trial, the degree of pain will be evaluated using a VAS according to the plan (Fig. 1). After SCS system implantation, assessment items will be evaluated according to the plan, including the degree of improvement with respect to pain relief and mental state (Table 2).

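### Secondary outcome (4): the complete-case rule discards participants already known to have failed, and nine predictors (15 to 25 parameters) meet at most 46 patients in the smaller outcome class

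*Protocol article*

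**What the plan says.** All references are to the protocol article.

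- **Analysis set** (Statistical analysis): "In participants with no missing VAS values preoperatively to 12 months after implantation, analyses of the prognostic factors". A gap at 18 or 24 months does not exclude a participant.
- **Model** (same section): a logistic analysis with nine explanatory variables, "treatment group, pre-implantation VAS value, sex, age, causative disease, site of pain, degree of paralysis, degree of sensory disturbance, and disease duration". No reduction step, merging of categories or penalization is given.
- **Outcome** (Secondary outcomes): efficacy is a VAS fall of at least 33% from the value before implantation, and the long-term effect is that efficacy continuing for more than 12 months. VAS is recorded preoperatively and at 1, 3, 6, 12, 18 and 24 months.
- **Categories** (Clinical assessments): causative disease is "central post-stroke pain, post–spinal cord injury pain, failed back surgery syndrome, complex regional pain syndrome, post-herpetic neuralgia, diabetic neuropathic pain, peripheral arterial disease, or others"; the others are "location of pain (arm, leg, lower back, back, chest, face", "degree of paralysis (none, mild, moderate, severe" and "sensory disturbance (hypoesthesia, allodynia, numbness".
- **Numbers** (Sample size; Study procedures): 92 participants are enrolled, and only those with pain relief in the SCS trial go on to implantation.
- **Missing data**: for the primary outcome a missing value counts as no improvement; otherwise nothing is imputed.
- **Caveat** (Discussion): outcomes (3) and (4) cover responders only and are offered as reference material.

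**The concern.** Two features of a stated rule work against the question it is meant to answer.

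First, the analysis set depends on completeness in a way that treats the two outcomes differently. A sustained effect can be confirmed only with every visit present. Loss of effect can be confirmed by a single visit. Requiring every visit therefore throws away some outcomes that are known, and all of those are failures.

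Second, the predictor list is long for the number of patients who can reach this analysis. A maximum-likelihood logistic model fitted this way tends to show good apparent discrimination that is not real, to give infinite or unstable odds ratios for sparse categories, and to name predictors by chance.

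At stake is the credibility of any reported predictor of long-term benefit, which the abstract lists as a secondary outcome.

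**Working it through.** **1. The plan's own figure.** The only sample size stated is for the primary comparison: 80% versus 50%, significance level 0.05 (two-sided assumed), power 80%. With pooled variance and no continuity correction, n per arm = [1.960·√(2·0.65·0.35) + 0.842·√(0.80·0.20 + 0.50·0.50)]² / 0.30² = 38.5, so 39 per arm and 78 in total. This reproduces the stated 78. Enrolment is 4 × 23 = 92. No event count is given for the predictor model.

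**2. Who the complete-case rule removes.** Visits up to 12 months, with the effect required to continue:

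| VAS record to 12 months | Outcome | In the planned analysis? |
|---|---|---|
| Complete, at least 33% reduction throughout | Success | Yes |
| Complete, at least one visit below 33% | Failure | Yes |
| Gap, and an observed visit below 33% | Failure, already known | **No** |
| Gap, all observed visits at least 33% | Undetermined | No |

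The third row is the fault. No participant with a gap can be a confirmed success, so every known outcome that the rule discards is a failure.

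**3. Parameters**, from the listed categories (levels minus one):

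| Variable | Full dummy coding | Leanest | Largest |
|---|---|---|---|
| Treatment group | 2 (three patterns) | 1 (new vs tonic) | 3 (four sequences) |
| VAS, sex, age, duration | 4 | 4 | 4 |
| Causative disease (8 levels) | 7 | 7 | 7 |
| Site of pain | 5 (6 locations) | 1 (central/peripheral) | 5 |
| Paralysis | 3 | 1 (ordinal) | 3 |
| Sensory disturbance | 2 | 1 (score) | 3 (separate items) |
| **Total** | **23** | **15** | **25** |

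**4. Smaller outcome class per parameter.** The smaller class limits a logistic model, and it is at most 92/2 = 46.

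- Best case (all implanted, complete, evenly split): 46/23 = 2.0; 46/15 = 3.1; 46/25 = 1.8.
- Assumed 80% implanted and 10% incomplete: 92 × 0.8 × 0.9 = 66 patients. An even split gives 33, or 33.1/23 = 1.4. If 30% fall in the smaller class it is 20, or 19.9/23 = 0.9. At 15 parameters: 2.2 and 1.3.
- Assumed 50% implanted and 20% incomplete: 92 × 0.5 × 0.8 = 37 patients. An even split gives 18, or 18.4/23 = 0.8. At 15 parameters: 1.2.

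**5. What that does.** A simulation with no true predictors used independent covariates, equally frequent categories and 300 datasets per setting. A fit counted as failed if it did not converge or gave extreme coefficients or standard errors; the other columns use the remaining fits.

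| Parameters, n, outcome rate | Failed fits | Apparent AUC | False positives per coefficient | Global test rejects |
|---|---|---|---|---|
| 23, 92, 50% | 4% | 0.79 | 8.7% | 15% |
| 23, 74, 30% | 50% | 0.85 | 7.7% | 15% |
| 23, 46, 50% | 88% | 0.88 | (few fits left) | (few fits left) |
| 15, 92, 50% | 3% | 0.73 | 5.2% | 9% |

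The true AUC is 0.50 in every row and the nominal error rate is 5%.

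**The case against.** The strongest reply is that the article already disclaims this outcome. The Discussion says that outcomes (3) and (4) are not a fair assessment and that identifying predictors needs a separate, well-designed study. That stands, and it lowers the weight of the point. But the reason it gives is the restriction to responders; it mentions neither the loss of known failures nor the number of parameters.

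It is also fair that coding is not fixed and may be settled in an analysis plan not shown here. Hence the range of 15 to 25; the ratio is low throughout.

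Several stronger readings are tempting but not supported:

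- **At most 46 events.** The 46 caps the smaller class. Sustained responders could exceed it: if 90% of 92 are implanted and 70% of those keep the effect, there are 92 × 0.9 × 0.7 = 58.
- **The predictors would be mostly noise.** The true effects are unknown. In the simulation at 23 parameters and n = 92, 78% of fits had at least one p < 0.05, but 23 independent tests at 5% would give 1 − 0.95²³ = 69% with any amount of data. The failure rates depend on assumed category frequencies and sample sizes.
- **The long-term response rate would be overstated.** The article plans no response proportion from this set. If missingness depended on the outcome alone, the logistic slopes would not be biased, only the intercept. Bias in the slopes needs missingness related to both outcome and predictors, which is plausible but not shown.
- **The 24-month mixed model throws away earlier visits.** The words "the 24-month analysis will be performed at 18 months and the final follow-up (24 months" can be read that way. But the same section first describes a model over all visits from 1 to 24 months, and its opening paragraph sets out when each data cut is analysed. The sentence may only name the time points reported.

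**Conclusion.** The point holds for secondary outcome (4). The stated analysis set discards participants whose failure is already established. This rests on reading a continuing effect as one present at every visit up to 12 months. The cost is lost information and possible bias in the predictor estimates; its size cannot be given, because the article states neither the implantation rate nor the expected missingness.

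The stated model is too large for the data under any reasonable coding: at most 2.0 patients in the smaller class per parameter with full dummy coding and 3.1 at the leanest, and about 1 or fewer in several of the assumed implantation scenarios. Optimistic discrimination, separation and chance predictors are to be expected.

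This is a moderate point about an exploratory secondary analysis. The primary outcome and the SCS-trial comparisons are untouched.

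**What to change.** - **Analysis set.** Include all implanted participants whose outcome is determined by observed data. Count an observed loss of the 33% reduction at any visit up to 12 months as no long-term effect, even if other visits are missing. Keep the complete-case analysis as a sensitivity analysis. Because those with a gap and no observed loss remain undetermined, report how many there are and show the result with them counted each way.
- **Model.** Use penalized logistic regression (for example Firth). Merge sparse disease and site categories in advance, without sight of the outcome, and state the coding of "causative disease, site of pain, degree of paralysis, degree of sensory disturbance, and disease duration" and of treatment group. Retain causative disease, since which pattern suits which kind of pain is the trial's second clinical question.
- **Reporting.** Label the result exploratory, and add the missing-visit selection and the ratio of patients to parameters to the caveat in the Discussion.
- **Minor clarification.** State that the 24-month mixed model uses all post-implantation visits, with 18 and 24 months as the time points reported.

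The cost is a change of wording, slightly more analysis work and less detail by category. No design or data-collection change is needed, and recruitment runs to March 2028, so it can be settled before the 12-month analysis.

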### Study procedures

This trial consists of two steps. The first step is an SCS trial, and the second step is SCS system implantation. In the SCS trial, two cylinder-type leads (Model 977A190; Medtronic Inc.) will be inserted under local anesthesia and connected to an external stimulation device, and intraoperative stimulation will be performed to confirm the area of paresthesia induction. The leads will be placed at vertebral levels of the paresthesia covering the painful area and then directly sutured to the skin at the puncture sites without a skin incision. During the SCS trial, three stimulation patterns, tonic, DTM, and FAST, will be applied. After the SCS trial ends, the inserted leads will be removed in all cases. If pain relief effects are obtained in the SCS trial, the cases will proceed to the second step. More than 1 month after the SCS trial, new cylinder-type leads and an implantable pulse generator (IPG) will be implanted under general anesthesia referring to the previous X-ray of the SCS trial lead placement. The type of implanted devices will be determined as follows: leads (Model 977A190; Medtronic Inc.) and IPG (Intellis; Medtronic Inc.) will be implanted if the DTM stimulation pattern is effective; leads (Linear ST lead; Boston Scientific) and IPG (WaveWriter Alpha 32; Boston Scientific) will be implanted if FAST or tonic stimulation patterns are effective.

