### Secondary outcomes

The following secondary outcomes will be analyzed at the end of the SCS trial: (1) the relationship between causative disease and improvement rates by each stimulation pattern and (2) comparison of the improvement rates between DTM and FAST stimulation patterns in all cases and by causative disease.

After SCS system implantation, the efficacy of SCS is defined as when the VAS value decreases by 33% or more compared to the VAS value before the implantation. Long-term effect is defined as continuing the efficacy of SCS for more than 12 months. The following secondary outcomes will be assessed for six times during 24 months’ follow-up periods after the implantation (Table 2): (3) changes in assessment items including the VAS, SF-MPQ-2, PCS, and QIDS-J preoperatively, and at 1, 3, 6, 12, 18, and 24 months after the implantation; (4) preoperative factors associated with the long-term effects; and (5) adverse events related to this study 3 months after the SCS system implantation. Data will be presented as mean and standard deviation for continuous variables (including VAS score, SF-MPQ-2 score, PCS score, and QIDS-J score).

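### Secondary outcome 4 uses the pre-implantation VAS both as the reference value of the outcome and as a listed prognostic factor, so shared measurement error pushes its odds ratio upward.

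*Protocol article*

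**What the plan says.** The Secondary outcomes section of the protocol article states that, after implantation, "the efficacy of SCS is defined as when the VAS value decreases by 33% or more compared to the VAS value before the implantation". It adds: "Long-term effect is defined as continuing the efficacy of SCS for more than 12 months". Assessments are scheduled "preoperatively, and at 1, 3, 6, 12, 18, and 24 months after the implantation".

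The Statistical analysis section then plans "analyses of the prognostic factors related to the long-term effect of continuing 33% reduction in the pain VAS over 12 months". The analysis set is restricted: "In participants with no missing VAS values preoperatively to 12 months after implantation". The method is "logistic analysis with the following explanatory variables: treatment group, pre-implantation VAS value, sex, age, causative disease, site of pain", followed by degree of paralysis, degree of sensory disturbance and disease duration. Pre-implantation VAS stands in this list on the same footing as the other variables.

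Two earlier VAS readings are described. Eligibility uses a "Pain visual analog scale (VAS) score" above 40, and the Method of SCS trial section schedules a reading before Stim-1. Only some participants reach the long-term analysis: "If pain relief effects are obtained in the SCS trial, the cases will proceed to the second step".

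The Discussion says that outcomes 3 and 4 are for reference only, because non-responders are not included in them.

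**The concern.** One reading serves two purposes. It is the denominator of the percentage fall that defines success, and it is a candidate predictor of success. Random error in that reading therefore enters both sides of the regression with the same sign. This is mathematical coupling, a form of regression to the mean.

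In the primary model a pre-stimulation VAS also appears, but there it only adjusts a treatment comparison and nobody needs to read its coefficient. In the model for outcome 4 the coefficients are themselves the result. A report that greater pre-implantation pain favours lasting benefit could then be partly or wholly an artefact, and it is the kind of statement readers carry into patient selection.

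Both the outcome definition and the covariate list are fixed in the article, so this is a stated choice and not a detail left to an analysis plan.

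**Working it through.** The article gives no figure for this model, so there is none to reproduce. The check has an algebraic part and a simulated part.

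**Algebra.** Let T be true pain before implantation, R the true proportional relief, e0 the error in the pre-implantation reading and e_v the error at visit v.

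- Observed baseline: B = T + e0.
- Observed follow-up: F_v = T(1 − R) + e_v.
- Success at visit v: F_v ≤ (1 − 0.33)B = 0.67B.
- Substituting: e_v − 0.67·e0 ≤ T(R − 0.33).

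Three things follow.

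1. With no error, success depends only on whether R ≥ 0.33. If R is unrelated to T, baseline pain has no association with success.
2. A positive e0 makes success easier and also raises B. This is the shared-error path. Example with an assumed true VAS of 65: read correctly, the target is 0.67 × 65 = 43.55 mm, a true fall of 33%. Read as 75, it is 0.67 × 75 = 50.25 mm, a true fall of 1 − 50.25/65 = 22.7%. Read as 55, it is 0.67 × 55 = 36.85 mm, a true fall of 43.3%.
3. T multiplies the margin R − 0.33, so a given follow-up error in mm matters less at high T. This second path uses no shared reading.

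**Simulation, percent relief unrelated to baseline.** Assumptions not in the documents: true VAS mean 65, SD 15; relief mean 50%, SD 25%; enrolment reading above 40; about 70 patients; equal independent error at every reading. The model is a univariable logistic regression, and false positives are counted at two-sided 5%. Success is required at 1, 3, 6 and 12 months.

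| VAS error SD | Odds ratio per 10 mm | False positives |
|---|---|---|
| near 0 | 0.99 to 1.01 (60 or 75 patients) | 4% to 5% |
| 5 mm | 1.17 | 12% |
| 8 mm | 1.30 | 34% |
| 12 mm | 1.42 | 64% |
| 5 to 12 mm, separate baseline reading as predictor | 1.08 to 1.09 | 5% to 9% |

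Judged at 12 months only, with error SD 5 to 12 mm, the odds ratio is 1.10 to 1.31 and false positives are 7% to 37%.

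**Other distributions.** With true VAS mean 70 (SD 15), and relief mean 33% to 60% and SD 20% to 30%, the four-visit odds ratio is 1.11 to 1.21 at 5 mm error, 1.24 to 1.39 at 10 mm and 1.33 to 1.48 at 15 mm. At 10 mm, with relief mean 50% and SD 20%, success by tertile of observed baseline is 41%, 56% and 66%, although true percent relief does not depend on baseline.

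**Separating the two paths.** With baseline error removed and follow-up error of 5 to 15 mm kept, the four-visit odds ratio is still 1.07 to 1.24 in these other distributions.

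**Millimetre relief unrelated to baseline** (mean 32.5 mm, SD 16; four visits). The success condition becomes e_v − 0.67·e0 ≤ D − 0.33T, where D is relief in mm, so higher pain needs more mm of relief.

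| VAS error SD | Same reading | Separate reading |
|---|---|---|
| 0 | 0.70 | – |
| 5 mm | 0.80 | 0.75 |
| 8 mm | 0.91 | 0.79 |
| 12 mm | 1.06 | 0.85 |

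The shared reading raises the odds ratio at every error size, but mostly not above 1.

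**The case against.** The strongest reply is that the predicted artefact depends on the null chosen. The document does not say how relief scales with baseline pain. Under constant millimetre relief the trial would mostly not report that patients with more pain do better. This stands. A reader might infer that measurement error alone will make high pre-implantation pain look favourable, and the documents do not support that. They support only an upward bias.

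A reader might also infer that the shared reading is the sole cause, because the odds ratio returns to about 1.0 when error is near zero. That comparison removes baseline and follow-up error together. Follow-up error alone leaves part of the four-visit bias, so this inference fails too. Nor has it been shown that the coefficients of the other predictors are distorted, since the calculations above are univariable.

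The consequence is limited. This is one coefficient in a secondary analysis that the Discussion already calls reference only. The reason given there is the restriction to responders, however. That reason neither mentions nor cures the coupling, and a reader so warned could still take the VAS coefficient at face value.

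Finally, the content of Table 2 is not shown, and the text does not date the pre-implantation reading. If it is the enrolment VAS, that reading cannot serve as the separate predictor. This limits one of the substitutes but not the point.

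**Conclusion.** The point holds in a limited form. As planned, the odds ratio for pre-implantation VAS in the outcome 4 model is biased upward by error that it shares with the outcome. Under the percent-relief null, with error SD 5 to 12 mm and about 70 patients, the false-positive rate runs from about twice the nominal 5% to well over half if success is required at all four visits. It is smaller, and near nominal at 5 mm, if judged at 12 months only. The wording on continuing the reduction fits the four-visit reading better but does not settle it.

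The error size, the pain and relief distributions and the number analysed are all assumed, so these ranges show what could happen and do not size the problem for this trial. The direction of the bias was the same under both nulls. The primary comparison is not touched. The point should be corrected before the 12-month analysis.

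**What to change.** In the Statistical analysis section, in the item on long-term effect:

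- Keep the pre-implantation VAS as an adjustment term only, and state that its coefficient will not be reported or interpreted as a prognostic factor.
- If pain level is to be assessed as a predictor, use an earlier VAS that is not the outcome's reference reading. This can be the enrolment VAS, if that is a different reading, or the pre-Stim-1 VAS. The latter is taken after lead insertion and may not represent usual pain, which should be noted.
- State which reading is the pre-implantation VAS.

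Swapping the reading removes the shared-error path but not the part due to follow-up error, so a modest upward bias can remain (odds ratio 1.08 to 1.09 in the first simulation). The first option avoids the issue altogether.

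The cost is a few sentences: one covariate is no longer interpreted, or is replaced. The text already provides for both earlier readings, so no new data should be needed.
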